#### Safety assessment

The participants are instructed to report any adverse events which may occur while taking the interventions. All possible adverse events will be described in the CRF. The investigator will withdraw any participant experiencing a serious adverse event. This will be reported to the MFDS within 15 working days of withdrawal according to the Korea Good Clinical Practice (KGCP) guidelines. Participants who have withdrawn will receive appropriate treatment. The investigator will have full responsibility for the safety of participants. For safety assessments, a liver function test, blood cell count test, physical examination, and urine analysis will be conducted at baseline and at visit 5. Any loss caused by the trial will be reimbursed via insurance. The safety datasets will include the participants who are administered Euiiyin-tang or placebo at least once. The incidences of physical examination and self-reported adverse events will be compared using a chi-square test. A liver function test, blood cell count test, and urine analysis will be compared between the groups. The data will be categorised into either normal or abnormal groups according to their respective normal ranges. Differences between the groups will be assessed via a chi-square test.

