### Study objectives

The main objectives of the present study are (1) to evaluate the efficacy and safety of Euiiyin-tang in obese Korean female adults and (2) to detect the correlations between obese participants and the Taeum classification of Sasang constitutional medicine.

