### Sample size

The sample size calculation is based on weight change between baseline (visit 2) and after treatment (visit 5). The hypothesis is as follows:$$ {\mathrm{H}}_0:\updelta =\Delta 1\hbox{-} \Delta 2=0 $$
$$ {\mathrm{H}}_1:\updelta =\Delta 1\hbox{-} \Delta 2\ne 0 $$where Δ1 = Weight change between visit 5 and baseline in Euiiyin-tang group

Δ2 = Weight change between visit 5 and baseline in placebo control group.

In a study by Heymsfield et al. [23], the standard deviation (SD) in weight reduction of the groups is 3.9. We assume that both groups will have an equivalent SD. The effect size of this study is hypothesised to be 0.5 as the moderate effect. Consequently, the difference in weight change between groups is assumed to be 1.95. The allocation ratio is 1:1. The following formula is used to estimate the sample size [24]:$$ \mathrm{m}=\left(\frac{1+\psi}{\psi}\right)\kern0.24em \frac{{\left({\mathrm{z}}_{1\hbox{-} \frac{\upalpha}{2}}+{\mathrm{z}}_{1\hbox{-} \beta}\right)}^2}{\varDelta^2}+\frac{{{\mathrm{z}}^2}_{1\hbox{-} \frac{\upalpha}{2}}}{2\left(1+\psi \right)} $$where *m* = the sample size of one group$$ \uppsi =\mathrm{the}\;\mathrm{allocation}\;\mathrm{ratio} $$
$$ \upalpha =0.05,\upbeta =0.8 $$

After taking into account the dropout rate of approximately 20%, the sample size for each group is 80 participants, to allow the test to remain within 5% of the two-sided significance level and possess 80% statistical power. Therefore, the total sample size of this trial is 160.

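### Safety is a main objective, but the only stated between-group analysis is a chi-square test, which gives no estimate or bound and has little power for uncommon events

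*Protocol article*

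**What the plan says.** The protocol article's Study objectives section puts efficacy and safety together in the first main objective: "to evaluate the efficacy and safety of Euiiyin-tang in obese Korean female adults".

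The Safety assessment section under Statistical analysis gives the comparative method. For adverse events and examination findings: "The incidences of physical examination and self-reported adverse events will be compared using a chi-square test". For the liver function, blood count and urine results: "The data will be categorised into either normal or abnormal groups according to their respective normal ranges", and then "Differences between the groups will be assessed via a chi-square test". The analysis population is everyone dosed: "The safety datasets will include the participants who are administered Euiiyin-tang or placebo at least once". The section names no effect estimate, interval or bound.

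The Sample size section works from weight change alone. It arrives at this: "the sample size for each group is 80 participants". Neither section gives an expected adverse-event rate.

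**The concern.** A chi-square test of equal proportions answers one question: are the data surprising if the two arms have the same event rate? A small p-value is a signal of harm. A large p-value may mean that the rates are close, or that the trial is too small to tell, and the test cannot separate the two. For a safety objective the useful quantity is how much excess risk the data still allow, and the stated method does not produce it.

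The Background says that no human studies of this formula in obesity have been reported, and it refers to a public perception that herbal medicines have fewer adverse effects. In that setting, a table of non-significant p-values for individual adverse events and laboratory abnormalities could easily be taken as reassurance, although the data might not exclude a several-fold increase in an uncommon event.

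**Working it through.** **Inputs from the protocol article.** 80 per arm, 1:1 allocation, two-sided 5% level, 80% power, effect size 0.5 (1.95 with SD 3.9) and about 20% dropout, all from Sample size. The chi-square test is from Safety assessment.

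**Assumed, because the article gives no value.** The placebo event rate is varied from 2% to 30%. The 64-per-arm rows show visit 5 laboratory data if the full 20% were missing (80 × 0.80 = 64).

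**Step 1: reproduce the stated sample size.** With ψ = 1 the article's formula is m = 2(1.96 + 0.842)²/0.5² + 1.96²/4 = 62.79 + 0.96 = 63.75, so 64. Then 64/0.80 = 80 per group and 160 in total, as stated. This size is for weight change and says nothing about power for adverse events.

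**Step 2: chance that the chi-square test misses a true increase.** For independent binomial counts in the two arms, all possible 2×2 tables were enumerated. The probabilities of tables with an uncorrected Pearson statistic above 3.84 in the direction of harm were summed; the miss rate is 1 minus that sum.

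| Placebo vs drug (assumed) | Missed, 80 per arm | Missed, 64 per arm |
|---|---|---|
| 5% vs 10% | 79% | 82% |
| 10% vs 20% | 58% | 65% |
| 12.5% vs 25% | 47% | 56% |
| 15% vs 30% | 37% | 47% |
| 20% vs 40% | 20% | 29% |
| 30% vs 60% | 3% | 7% |
| 2% vs 6% | 78% | 81% |
| 5% vs 15% | 43% | 51% |

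A continuity correction raises the miss rates: at 80 per arm, to 87% for 5% vs 10% and 66% for 10% vs 20%.

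**Step 3: where a doubling becomes more likely found than missed.** Power for a doubling reaches 50% at a placebo rate of about 12% with 80 per arm, and about 14.5% with 64. It reaches about 80% at a placebo rate of 20% with 80 per arm.

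**Step 4: what an interval would show and the p-value does not.**

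- *A non-significant result.* Suppose 10/80 on drug and 4/80 on placebo. χ² = 160 × (10×76 − 4×70)² / (80 × 80 × 14 × 146) = 2.82, p = 0.093. The risk difference is 12.5% − 5.0% = +7.5 points. The Wilson limits are 6.9% to 21.5% and 2.0% to 12.2%, so the Newcombe 95% interval is −1.6 to +17.0 points. The test reports no significant difference; the interval shows that an excess of up to 17 points is not excluded.
- *Equal observed rates at 80 per arm.* The simple large-sample upper limit for the difference is 1.96 × √(2p(1−p)/80). That is +6.8 points at 5%, +9.3 at 10% and +12.4 at 20%. The matching upper limits for the risk ratio are 3.9, 2.5 and 1.86.
- *No events in 80 women.* The upper limit of the exact two-sided 95% interval is 1 − 0.025^(1/80) = 4.5%.

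**The case against.** The strongest reply is that the article sets no rule for declaring safety. It says that incidences will be compared, so the incidences by arm will be available. Naming a chi-square test does not forbid an interval, and intervals may appear in the full protocol or analysis plan, which are not shown. A placebo-controlled superiority trial is ordinarily sized on efficacy, with no safety margin, and limited information on uncommon harms is common to trials of this size.

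Much of that stands. Three stronger readings are tempting, and none is supported:

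- **That the plan treats non-significance as proof of safety.** The article nowhere says so. That would be a later misreading, not a stated rule.
- **That a doubled or tripled event rate would usually be missed, whatever the event.** This depends on a placebo rate that the article does not give. At 80 per arm, 20% vs 40% is detected about 80% of the time, and even 5% vs 15% is detected more often than not (missed 43%). The overall proportion of women with any adverse event may therefore be compared with adequate power.
- **That the trial should have had a safety margin or been sized for safety.** Neither is a usual requirement for this design.

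The choice of method is not answered. The article does not leave the safety comparison to another document; it names the chi-square test twice, as the only between-group analysis, for an outcome in a main objective. Raw incidences by arm give a point estimate to anyone who subtracts them, but no bound on the excess risk.

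**Conclusion.** The point holds as an inexpensive improvement, and its force is limited to uncommon events. The stated safety comparison can flag a harm but gives no estimate or bound on which a favourable safety conclusion could rest. At 80 per arm, and on assumed placebo rates, it would miss a doubling about 79% of the time from 5% and about 58% from 10%. Below a placebo rate of about 12% (about 14.5% if only 64 per arm contribute) a doubling is more likely missed than found; above that it is more likely found. These figures assume independent binomial counts and an uncorrected test; a continuity correction makes them worse. The sample size and the absence of a safety margin are not faults.

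**What to change.** Amend the Safety assessment section of the statistical analysis as follows:

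1. For each adverse-event category, examination finding and laboratory abnormality, report the between-arm risk difference with its 95% Newcombe (score) interval, and make this the basis of the safety comparison.
2. For events not seen in the drug arm, report the exact upper 95% limit of the rate.
3. Keep chi-square p-values as descriptive flags only.
4. Add a sentence saying that a non-significant difference will not be taken as evidence of safety, and that the conclusion will state the largest excess risk the data do not exclude.

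The cost is a wording change and a few lines of analysis code. No new patients, visits or measurements are needed. The small downside is a more cautious safety conclusion. The change does not add power for uncommon harms; it makes the remaining uncertainty visible.

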### Data and safety monitoring

The KCRD will monitor the clinical trial. The monitoring will begin once the first participants complete the required number of visits. All investigational institutions will be monitored based on the SOPs while this trial is in process. Auditing is not scheduled for the present study. To improve data quality, range checks for data values and double data entry will be conducted. Any other committee such as a coordinating centre, steering committee, or endpoint adjudication committee will not be applicable to the present study.

### Ethics and dissemination

This trial is conducted to comply with the Declaration of Helsinki 2008 and/or the regulations of the GCP principles in the Korean MFDS. This trial has received the approval of the institutional review boards (IRBs) of all three institutions: the IRB of Gil Korean Medical Hospital, Gachon University (11–105), the IRB of the Catholic University of Korea Seoul St. Mary's Hospital (KIRB-00393-002), and the IRB of Korean Medical Hospital of Sangji University (SJ IRB 120607). The current protocol is version 1.5, and it is developed according to the SPIRIT checklist (see Additional file 1). All items have been drawn from the World Health Organisation (WHO) Trial Registration Data Set (see Additional file 2). Written informed consent will be obtained prior to the study by the investigator (see Additional file 3). Moreover, we have contracted liability insurance for patient safety. The confidentiality of personal information will be ensured. Each participant will be assigned a trial identification number at enrolment. For the duration of the entire trial, data will be handled based on the trial identification number. All records will remain secure in a locked cabinet or password-protected computer files, both for the duration of the trial and after the trial has concluded. Only investigators will retain the right to access the data. The results of the present study will be disseminated through scientific journals or scientific conference presentations. So far, no public access to the full protocol, participant-level datasets, or statistical code is planned.

## Discussion

The present study investigates the clinical efficacy and safety of Euiiyin-tang in the treatment of patients with obesity. Currently, the increasing prevalence of obesity is a public health concern in many developed countries [29]. The increasing prevalence of obesity is a consequence of social changes leading to the increased consumption of high calorie foods and a reduction in physical activity [30].

Some medical surgeries, such as liposuction and gastric banding, and pharmaceutical agents such as sibutramine, are attributed to certain complications and side effects. Consequently, many patients with obesity seek non-invasive and safer alternative treatment. Therefore, herbal medicine made from natural products has received noticeable attention in obesity treatment [31, 32]. Among these medicines, Euiiyin-tang has been attributed to weight loss in clinical practice [33], but there is little evidence to support this. We obtained an Investigational New Drug (IND) approval from the MFDS to conduct the present clinical trial on Euiiyin-tang.

A previous study on Taeumjowi-tang in patients with obesity resulted in a statistically insignificant primary outcome [31]. In the study, the primary endpoint was the percentage of participants with a weight loss of 5% compared to baseline. However, the study used a strict standard, and consequently did not produce a meaningful conclusion. Therefore, we compared weight changes after the administration of the treatment in each group. The SD value was obtained from Heymsfield et al. [23]. The effect size of 0.5 was derived based on agreement between researchers.

Herbal medicines have been used to treat obesity over long periods of time. However, as the duration of a clinical trial increases, the participant dropout rate increases likewise. As a result, we decided to conduct the follow-up after 12 weeks to confirm significance and to minimise the dropout rate. The study period was adapted from Heymsfield and the previous study on Taeumjowi-tang [23, 34].

Although the present study was limited by permitting only adult women as participants, it nonetheless has several distinctive features. First, it is the only randomised, controlled trial thus far to investigate the efficacy of Euiiyin-tang in the treatment of obesity. In the present study, we will assess not only weight reduction, but also the quality of life and stress through questionnaires. Second, this study will investigate the correlation between obesity and Sasang constitutional medicine, which is a distinct concept of Korean medicine.

In conclusion, the purpose of the present study is to evaluate the efficacy and safety of Euiiyin-tang, which is often used to treat weight loss. We expect that the present study will act as a reference for designing further clinical trials to assess herbal medicine in the treatment of obesity.

## Trial status

Participant recruitment began on 26 April 2013, and 149 participants have been recruited thus far.

## Abbreviations

5-HIAA: 5-Hydroxyindoleacetic acid
5-HT: 5-Hydroxytryptamine
ANOVA: Analysis of variance
ATC: Anatomical Therapeutic Chemical
BMI: Body mass index
BMR: Basal metabolic rate
CRF: Case report form
CRO: Contract Research Organisation
CRP: C-Reactive protein
DOPAC: Dihydroxyphenylacetic acid
IND: Investigational New Drug
IRB: Institutional review board
ITT: Intention-to-treat
KCRD: Kyung Hee University Centre for Clinical Research and Drug Development
KEAT-26: Korean version of Eating Attitudes Test
KGCP: Korea Good Clinical Practice
KOQOL: Korean version of Obesity-related Quality of Life
LOCF: Last-observation-carried-forward (analysis)
MFDS: Ministry of Food and Drug Safety
PP: Per-protocol
QSCCII: Questionnaire for Sasang Constitution Classification II
SD: Standard deviation
SOP: Standard Operating Procedure
SRI: Stress Reaction Inventory
SRRS: Social Readjustment Rating Scale
WHR: Waist-to-hip ratio
